### **Data management**

Data collected during visits would be checked for accuracy and completion by supervisors.

Data would be double entered into computer using Visual Foxpro software. Verification checks will be done to correct the discrepancies in records.

### **Statistical Analysis**

Baseline and evaluation survey data will be analyzed to assess changes in each outcome in both intervention and control arms. To minimize overestimation of the intervention effect, all intervention impact outcomes will be estimated by intention-to-treat analysis, by which individuals are analyzed according to an allocated arm as the outcome data are

available, regardless of the place where they received the care. Also, all eligible individuals are included in the analysis, whether or not they provided outcome data.

Data collected at the individual level will be analyzed using generalized estimating equations (GEE) and mixed effects models for both continuous and binary outcomes.

Adjustment factors include items such as basic demographic characteristics and socio-economic characteristics, as well as the characteristics of facilities located in the area where the mother and infant live. Data analysis will be done primarily using Stata version 12.1. (StataCorp LP, College Station, Texas, USA).

### **Problems Anticipated**

Participants' name will not be recorded, so no danger of potential privacy violations will be presented.

### **Ethical Considerations**

Ethical approval will be obtained from the Ethics Review Committee of the GHS, the Institutional Review Boards of Dodowa HRC, Kintampo HRC, and Navrongo HRC in Ghana, as well as the University of Tokyo in Japan. The implementation and research periods are estimated to span five years. Informed consent will be sought from all study participants and health workers before their inclusion in the study. **Especially for photographic and motion data, we will obtain consent on potential exposure of the data at public place, such as at national and international conference.** Permission will be sought from the local health authorities as well as from community leaders.

Study records will be identified by means of study IDs. Participants will be given the option to withdraw at any time during the study with the assurance that this will not affect

their normal service delivery at any of the health facilities.

### **Plan for Dissemination**

The results of the study will first be presented to community members and their leaders at HDSS sites. In addition, policy briefs will be developed in collaboration with the Policy, Planning, Monitoring and Evaluation Division of the GHS and submitted to the Office of the Director-General of GHS and to the Family Health Division. Presentations will be made at the GHS Directors meeting, the Senior Managers Meeting (SMM), as well as relevant international conferences. Papers based on the results will also be submitted for publication in peer-reviewed journals.

## In-depth Interview Guide for Women

## Overview

This is a guide to conduct an in-depth interview (IDIs) with women who participated in the EMBRACE intervention. The participants will be selected by convenience sampling. They will be recruited from Dodowa, Kintampo, and Navrongo intervention areas to respond to issues such as their attitude to continuum of care, health seeking behaviors, and health status. The interview will last for about 30 minutes, and the responses will be recorded using recorders to completely transcribe the voice data. After transcription, the voice data will be deleted.

## Objectives

To supplement the information collected from the quantitative survey

To grasp what made mothers to follow/unfollow the continuum of care

## Procedure

## Welcome, background information and introduction

Obtain informed consent

Fill out background information sheet

Conduct IDI

## Ghana EMBRACE Implementation Research – Intervention Evaluation

### In-depth Interview Guide for Women

*Information on data collection team*

|                     |  |
|---------------------|--|
| Interviewer's name: |  |
|---------------------|--|

|                    |  |
|--------------------|--|
| Note-taker's name: |  |
|--------------------|--|

|                     |  |
|---------------------|--|
| IDI venue: District |  |
| Community           |  |

|                     |  |
|---------------------|--|
| IDI date (DD/MM/YY) |  |
|---------------------|--|

|                |           |
|----------------|-----------|
| IDI start time | AM / PM : |
|----------------|-----------|

|              |           |
|--------------|-----------|
| IDI end time | AM / PM : |
|--------------|-----------|

# Ghana EMBRACE Implementation Research – Intervention Evaluation

## Background Information Sheet for IDI Participants

Interview Number:

|      |       |
|------|-------|
| IDI- | IDINB |
|------|-------|

Date of interview (DD/MM/YY):

|  |  |  |  |  |  |     |
|--|--|--|--|--|--|-----|
|  |  |  |  |  |  | DAT |
|--|--|--|--|--|--|-----|

1.1 Name of the village/community:

|     |
|-----|
| VIL |
|-----|

1.2 Location of residence:

|              |            |     |
|--------------|------------|-----|
| 0. Residence | 1.Farm hut | RES |
|--------------|------------|-----|

1.3 Age of the mother: (“88” when the respondent do not know her age)

|     |
|-----|
| AGE |
|-----|

1.4 Age of the infant (months): (“88” when the respondent do not know the age of her infant)

|        |
|--------|
| IAGE   |
| months |

1.5 Gender of the infant:

|         |          |      |
|---------|----------|------|
| 0. Male | 1.Female | ISEX |
|---------|----------|------|

1.6 Marital status:

|            |              |     |
|------------|--------------|-----|
| 1. Married | 2. Unmarried | MAR |
|------------|--------------|-----|

1.7 Education level:

|                                      |                                           |                               |     |
|--------------------------------------|-------------------------------------------|-------------------------------|-----|
| 1.No education                       | 2. Some years in
primary school | 3. Graduate
primary | EDU |
| 4. Some years in secondary
school | 5. More than secondary level              |                               |     |

1.8 Number of family members living together (a number except the respondent):

|      |
|------|
| NFAM |
|------|

1.9 Number of children living together:

|      |
|------|
| NCHI |
|------|

1.10 Family members living together (multiple choice):

|            |                   |                  |           |
|------------|-------------------|------------------|-----------|
| 1. Husband | 2. Farther-in-law | 3. Mother-in-law | FMEM      |
| 4. Father  | 5. Mother         | 6. Children      | 7. Others |

1.11 Occupation of respondent

|                                      |                               |     |
|--------------------------------------|-------------------------------|-----|
| 1. Farmer/laborer/domestic
worker | 2. House wife                 | ROC |
| 3. Profession: teacher, nurse,       | 4. Employed tradesman, driver |     |

|                                                      |                                |  |
|------------------------------------------------------|--------------------------------|--|
| accounts, administrator, etc                         | without own car, builder, etc. |  |
| 5. Trader/ businessman / driver
with own car etc. | 6. Clerical / secretarial      |  |
| 7. Other                                             |                                |  |

## Ghana EMBRACE Implementation Research – Intervention Evaluation

### Section 1: Socio-demographic characteristic and interview information

Self-introduction

### Section 2: Continuum of Care (CoC)

*Facilitator “I would like to ask about the CoC.”*

Do you know CoC? **Probe:** What are the contents of CoC? Why it is important?

**(For those who completed CoC)** What was your motivation for going antenatal care 4 times, giving birth at health facility, and going to PNC after birth? **Probe:** What is the benefit of having CoC?

**(For those who did not accomplish any of CoC)** What made you not receive antenatal care, delivery at facility, and postnatal care?

### Section 3: CoC card

*Facilitator “I would like to ask about the CoC card.”*

What do you think of CoC card? **Probe:** which parts do you like?

Did you talk about CoC card with others? **Probe:** did you talk with other pregnant women or husband? What did you talk?

Do you find any changes in this pregnancy, compared with previous one(s)? **Probe:** what? How? Why?

What does it mean to collect all the stars?

There were two different colours of stars in use (Gold and Orange). What is the difference between the gold stars and the orange stars?

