### ***Implementation impact outcomes***

The implementation impact outcomes are 1) acceptability of CoC card utilization and 2) feasibility of improved PNC rates within 48 hours postpartum by mothers' retention at the health facility or by home visits. These outcomes are to be compared before and after the intervention.

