### Section 4: Delivery and postnatal care

*Facilitator “I would like to ask you about delivery and postnatal care”*

Please tell me your experience from the start of labour to giving birth.

What do you think about giving birth at home? What do you think about giving birth at health facility? **Probe:**

How important is a health worker’s assistance (doctor, nurse, and midwife) during delivery?

What do you think about staying at health facility after birth?

**Probe:** If you stayed at health facility after deliver, what was the benefit? What was the difficulties?

What do you think of the postnatal care service?

**Probe:** If you stayed at health facility after deliver, what were the benefits?

What were the difficulties?

Have you received postnatal care at home? If yes, what do you think of that?

What do you think of your child’s health status?

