## **Interview guide**

### **Section 2: Continuum of care**

What changes have you found in mothers response to services since starting intervention (since introducing CoC card)?

Probe for:

What changes have you found in your service delivery as health workers since starting intervention (since introducing CoC card)?

How is interaction (relationship) between health workers and mothers since starting intervention (CoC card)?

What do you think of continue using CoC card?

What are mothers' reaction towards staying on at the health facility for 24 hours after delivery?

What is your opinion about the achievement of continuum of care from pregnancy to the postnatal period in this facility?

**Probe for:** Achievement of continuum of care from pregnancy to the postnatal period and reasons for lapses?

**Probe:** for positive and negative responses and for the period from pregnancy to the postnatal period when the continuum of care disrupted?

How would you assess the quality of maternal and child health services in your facility?

How acceptable are maternal and infant health services in your facility?

**Probe:** for positive and negative res

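### The women's interview guide follows its neutral question on the CoC card with a single probe, on what women like, and has no matching probe on dislikes, trouble or non-use

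*Protocol*

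**What the plan says.** Under Implementation impact outcomes, the protocol lists "acceptability of CoC card utilization" first of two outcomes. The Impact Evaluation section includes in-depth interviews with women and health workers in the data for judging implementation, together with supervision records of card distribution and use.

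The In-depth Interview Guide for Women covers the card in its Section 3. The opening question is "What do you think of CoC card", and the one probe under it is "which parts do you like". Four more lead questions follow: whether the woman discussed the card with others ("Did you talk about CoC card with others"), whether this pregnancy differed from earlier ones, what it means to collect all the stars, and how the two star colours differ.

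In Section 4 of the same guide, the probe on staying at the facility after birth asks "what was the benefit? What was the difficulties".

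**The concern.** A probe is what the interviewer turns to when the first answer is short or vague. If the only one provided asks for liked features, a woman with mixed or negative views is led to name something good, and nothing in the script leads her to name something bad. The card is meant to keep mothers in the full course of care. It stays with the mother and depends on providers adding stickers at each contact, so reasons why it was not understood, not brought or not used are what an acceptability assessment most needs. The guide's own aims include learning why mothers did or did not follow the continuum. At stake is how far the women's interviews can support a statement that mothers find the card acceptable.

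**Working it through.** No formula applies and the protocol gives no figure to reproduce. The check is a reading of every item on the card in both interview guides, set beside the guides' items on other topics.

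**Women's guide, Section 3 (card): five lead questions**

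| Lead question | Scripted probe | Direction |
|---|---|---|
| Opinion of the card | Liked parts | Stem neutral, probe favourable |
| Talked about it with others | With whom, and what was said | Neutral |
| Changes from earlier pregnancies | What, how, why | Neutral |
| Meaning of all the stars | None | Tests understanding |
| Difference between star colours | None | Tests understanding |

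Probes on opinion of the card: 1 favourable, 0 unfavourable. Items asking directly about dislike, trouble or reasons for non-use: 0 of 5 lead questions and 0 probes.

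**Women's guide, other sections**

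- Section 2 asks women who completed the continuum about benefit ("What is the benefit of having CoC"). It also asks women who did not take up the care what prevented them. Across the two groups, both directions are covered.
- Section 4 probes the facility stay twice, and each time asks for benefits and difficulties: 2 favourable, 2 unfavourable. Care at home gets a neutral question with no probe.

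**Health worker guide, Section 2**

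- "What do you think of continue using CoC card" is neutral and has no probe of its own.
- A further question asks how mothers' response to services has changed since the card was introduced.
- The probe "for positive and negative responses" is balanced, but it belongs to achievement of the continuum and not to the card.

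**What follows**

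1. The opinion stem lets a woman criticise the card, so negative content is possible.
2. The only scripted follow-up to that stem asks for positive content, so negative content depends on her initiative or on the interviewer improvising.
3. The authors had a two-sided form available and used it in the next section.
4. The supervision data can show that cards went unused, but not why from the mother's side. The health worker items give the provider's view of mothers' reactions.

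A lean in the women's interview evidence on this outcome therefore follows from the wording. Its size does not, because the protocol gives no number of interviews, no coding scheme and no expected answers.

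**The case against.** The strongest reply is that this is a topic guide for a conversation, and that the question women hear first is open. A mother who dislikes the card, or never used it, can say so before any probe. The questions on talking with others and on changes in this pregnancy are neutral and can also draw criticism. This stands. A reader might infer that the interviews cannot show the card to be unacceptable; the open stem rules that reading out.

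A reader might also infer that the guide never finds out whether the card was understood. That is not supported either: the two star questions can expose poor understanding, although they do not ask which parts were hard to follow.

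Nor is the card the sole departure from an otherwise balanced guide. The Section 2 probe for completers asks only about benefit, and Section 4 is not two-sided throughout. The comparison with the facility stay shows that balanced wording was at hand, not that it was the rule.

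Finally, acceptability does not rest on this probe. The guide describes the interviews as an addition to the quantitative survey, card use is counted during supervision, health workers are asked about the card, and the implementation outcomes are to be compared before and after the intervention. All of this limits the weight of the point. It does not remove it, because none of the sources described in the protocol is shown to ask mothers directly what was wrong with the card or why they did not use it.

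**Conclusion.** The point holds as a minor improvement. The scripted follow-up on the card is one-directional on a named implementation outcome, so the women's interview evidence leans favourable by an unknown amount. This assumes that interviewers follow the guide broadly as written; one who routinely adds the opposite probe would remove the lean.

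It would go too far to conclude that a finding of acceptability would be an artefact of the instrument. The lean concerns one strand of supplementary evidence, and the protocol gives no means of measuring it. The primary outcome, the other intervention impact outcomes and their analysis are untouched.

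**What to change.** In Section 3 of the women's guide, replace the single probe with a pair, for example: *Which parts were useful? Which parts were not useful, hard to understand or troublesome?* Add one question: *Were there occasions when the card was not brought or not used, and why?* The pair follows the form that Section 4 already uses for the facility stay.

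Adding difficulties to the benefit probe in Section 2 is optional, since that section already asks non-completers about barriers.

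The cost is a few lines of text and a minute or two in an interview of about 30 minutes. Sampling, survey and analysis do not change.

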### Section 4: Delivery and postnatal care

*Facilitator “I would like to ask you about delivery and postnatal care”*

Please tell me your experience from the start of labour to giving birth.

What do you think about giving birth at home? What do you think about giving birth at health facility? **Probe:**

How important is a health worker’s assistance (doctor, nurse, and midwife) during delivery?

What do you think about staying at health facility after birth?

**Probe:** If you stayed at health facility after deliver, what was the benefit? What was the difficulties?

What do you think of the postnatal care service?

**Probe:** If you stayed at health facility after deliver, what were the benefits?

What were the difficulties?

Have you received postnatal care at home? If yes, what do you think of that?

What do you think of your child’s health status?

## **Ghana EMBRACE Implementation Research – Intervention Evaluation**

### **In-depth interview guide for health workers**

#### **Overview:**

This is a guide to conduct in-depth interview (IDI) with trained health workers: doctors; nurses; midwives; and district public health nurse from community to district hospital level. Participants will be recruited from the Dodowa, Kintampo, and Navrongo Research Center Demographic surveillance areas to obtain information on issues related to changes in their attitudes and mothers' attitudes to continuum of care, as well as changes in health status of mothers and children. The interview will last for about 45 minutes, and their responses will be recorded using recorders to completely transcribe the voice data. After transcription, the voice data will be deleted.

#### **Objectives:**

To supplement the information collected from the quantitative survey

To obtain insight from health worker's side into the changes in attitudes to the continuum of care

To obtain insight from health worker's side into the changes in health status of mothers and children

#### **Procedure**

Obtain informed consent

Fill out background information sheet

Conduct IDI

#### **Section 1: Socio-demographic characteristics and interview information**

Fill out background information sheet

In-depth Interview Number:

|  |
|--|
|  |
|--|

 IDINBH  
W

Date of interview (DD/MM/YY):

|  |  |  |  |  |  |
|--|--|--|--|--|--|
|  |  |  |  |  |  |
|--|--|--|--|--|--|

 DAT

Starting time (HH/MM):

|  |  |  |  |
|--|--|--|--|
|  |  |  |  |
|--|--|--|--|

 STATM

Termination time (HH/MM):

|  |  |  |  |
|--|--|--|--|
|  |  |  |  |
|--|--|--|--|

 TRMTM

1.1 Type of participant

|                                  |                              |                              |      |
|----------------------------------|------------------------------|------------------------------|------|
| 1. District level health officer | 2. Obstetricians in hospital | 3. Midwives in health centre | TYPE |
| 4. CHOs and CHN                  | 5. TBA                       |                              |      |

1.2 Name of village

|  |
|--|
|  |
|--|

 VIL

1.3 Age: ("88" when the respondent do not know her age)

|  |
|--|
|  |
|--|

 AGE

1.4 Gender:

|         |           |     |
|---------|-----------|-----|
| 0. Male | 1. Female | SEX |
|---------|-----------|-----|

1.5 Education level:

|                                   |                                        |                            |     |
|-----------------------------------|----------------------------------------|----------------------------|-----|
| 1. No education                   | 2. Some years in primary school | 3. Graduate primary | EDU |
| 4. Some years in secondary school | 5. More than secondary level           |                            |     |

1.6 Years working at this position???for the actual post:

|  |
|--|
|  |
|--|

 YRSWP

## **Interview guide**

### **Section 2: Continuum of care**

What changes have you found in mothers response to services since starting intervention (since introducing CoC card)?

Probe for:

What changes have you found in your service delivery as health workers since starting intervention (since introducing CoC card)?

How is interaction (relationship) between health workers and mothers since starting intervention (CoC card)?

What do you think of continue using CoC card?

What are mothers' reaction towards staying on at the health facility for 24 hours after delivery?

What is your opinion about the achievement of continuum of care from pregnancy to the postnatal period in this facility?

**Probe for:** Achievement of continuum of care from pregnancy to the postnatal period and reasons for lapses?

**Probe:** for positive and negative responses and for the period from pregnancy to the postnatal period when the continuum of care disrupted?

How would you assess the quality of maternal and child health services in your facility?

How acceptable are maternal and infant health services in your facility?

**Probe:** for positive and negative res
